### Exclusion criteria

Class II obesity or morbid obesity (BMI of 35 kg/m^2^ or higher) according to published international standard charts for both adolescents and young women [73]Underweight (BMI < 18.5 kg/m^2^) or eating disorder (anorexia nervosa)Clinical suspicion or laboratory confirmation of anaemia or bleeding disorderEvidence of thyroid, liver, or kidney dysfunctionHistory of precocious puberty (breast development < 8.0 yr) or precocious menarche (menarche < 10.0 yr) [86]Clinical suspicion of Cushing syndromeEvidence of late-onset adrenal hyperplasia due to 21-hydroxylase deficiency [17-hydroxyprogesterone levels > 200 ng/dL in the follicular phase of the cycle or after 2 months of amenorrhea] [3, 13, 87]Hyperprolactinaemia (due to any cause including breast-feeding)Clinical suspicion or laboratory confirmation of glucose intolerance or diabetes mellitus [88, 89]Use of a medication affecting gonadal or adrenal function, or carbohydrate or lipid metabolism in the previous three months (including OCs)Gynaecological age < 2.0 yearsPositive pregnancy testPregnancy risk (failure to guarantee the use of non-hormonal contraception in sexually active subjects)Cardiac failure or history of cardiac failureHypersensitivity to a study drug or an excipientClinical suspicion of Addison’s diseaseClinical suspicion of any type of acute metabolic acidosis (i.e. lactic acidosis, diabetic ketoacidosis)Diabetic pre-comaAcute conditions with the potential to alter renal function such as dehydration, severe infection, shockAny disorder which may cause tissue hypoxia (especially acute disease or worsening of chronic disease) such as decompensated heart failure, respiratory failure, recent myocardial infarction, shockAcute alcohol intoxication or clinical suspicion of alcoholismClinical suspicion or laboratory confirmation of hyperkalaemiaConcomitant use of eplerenone or other potassium sparing diureticsConcomitant use of potassium-conserving diuretics and potassium supplementsCurrent bladder cancer or a history of bladder cancerNon-investigated macroscopic haematuria

### Who will take informed consent? {26a}

The principal investigator (PI) or their designee at each centre, in accordance with the institutional policy, will obtain an informed consent previously reviewed and approved by the responsible Ethical Committee (EC). A written consent form bearing the full name and signature of the patient or the patient’s parent/guardian and the assent of the patient (in case of minor patients), together with the name, date and signature of the local investigator, will be obtained. The signed informed consent constitutes a confidential document and therefore will be archived in the study binder. A copy of the consent will be given to the patient or patient’s parent/tutor.

### Additional consent provisions for collection and use of participant data and biological specimens {26b}

An additional written informed consent for biological sample collection and use of participant data will be obtained from the trial participants or the patient’s parent/tutor.

### Interventions

#### Explanation for the choice of comparators {6b}

Comparators were chosen according to the paediatric investigation plan (PIP) approved by EMA (002187-PIP01-17, approved on Feb 26, 2021):The Placebo arm is required for key comparisons with SPIOMET arm.The PIO arm allows to obtain hitherto scarce data with low-dose PIO in monotherapy in adolescent girls.The SPIO arm offers low-dose SPI an opportunity to disclose its additional effects, on top of PIO.

Indeed, many aspects of the current protocol design were agreed with PDCO as part of the aforementioned PIP.

#### Intervention description {11a}

The study medication consists of placebo tablets, PIO tablets, SPIO tablets and SPIOMET tablets manufactured by the pharmaceutical company Reig Jofre (Sant Joan Despí, Barcelona, Spain).

SPIOMET tablets have been manufactured with the same composition and process used to produce the SPIOMET tablet tested in phase I study [50]. PIO and SPIO tablets have been produced at the same facilities, using the same process and excipient composition as for SPIOMET, but replacing the amount of deleted active substances (MET 850 mg or MET 850 mg + SPI 50 mg), by an equivalent amount of suitable excipient that is unlikely to affect drug absorption. The proposed excipients are povidone (polyvinylpirrolidone) k-30, microcrystalline cellulose, croscarmellose sodium, polyglykol 4000 PS, magnesium stearate and purified water. Placebo tablets contain only the aforementioned excipients. Tablets containing placebo, PIO, SPIO and SPIOMET have the same size, shape and colour, ensuring the double-blind design of the study. The composition of the medication used in the clinical trial is detailed in Table 3.

**Table 3 Tab3:** Medication composition

	**Pioglitazone (7.5 mg)**	**Spironolactone (50 mg)**	**Metformin (850 mg)**	**Excipient**
Arm 1** Placebo**	No	No	No	1.1 g
Arm 2** PIO**	Yes	No	No	Up to 1.1 g
Arm 3** SPIO**	Yes	Yes	No	Up to 1.1 g
Arm 4** SPIOMET**	Yes	Yes	Yes	Up to 1.1 g

Patients in each study arm will take a tablet once a day, at dinner time, during meals. If needed, patients can break the tablet to facilitate the intake. There are no safety concerns or specific safety precautions for the intake of the medications. Missed doses should not be compensated. Postponement of medication intake is acceptable for up to 6 h; if postponement is > 6 h, then the dose should be skipped, and treatment should be continued on the next day. Missed doses should be reported in the patient’s diary.

During the active treatment phase spanning 12 months, a specific LIP will be implemented in 5 sessions that will coincide with the quarterly clinical visits (at 0, 3, 6, 9, 12 months), and will be led by a research nurse at each clinical centre.

#### Criteria for discontinuing or modifying allocated interventions {11b}

Study participants are free to withdraw from participation at any time upon request.

Discontinuation of the study intervention will imply discontinuation of the study and thus a dropout, so that any remaining study procedures will not be performed.

All data available until the discontinuation of the study intervention will be collected. If a clinically relevant finding is identified (including, but not limited to changes from baseline) after enrolment, the investigator or qualified designee will determine whether any change in participant management is needed. Any new clinically relevant finding will be reported as an adverse event (AE).

Criteria for discontinuing the allocated intervention are as follows: (1) pregnancy; (2) significant non-compliance with the intervention, for example, no medication intake for 30 consecutive days; in case of AE, patients are allowed to interrupt the treatment for 7 days without being withdrawn from the study; (3) any clinical AE, laboratory abnormality, or other medical condition/situation such that continued participation in the study is unlikely to be in the best interest of the participant; (4) appearance of an exclusion criterion (either newly developed or not previously recognised).

In case of premature termination of study participation, the patient will be re-allocated to the outpatient clinic as a regular patient whenever possible.

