### Sample size {14}

Numbers of patients in the four study arms have been calculated to attain 80% statistical power at two-sided 5% alpha level [90–92], with an expected dropout rate of 27%. The sample size is based on the two-sample *t*-test (R package “pwr”, functions “pwr.t.test” and “pwr.t2n.test”).

The number of subjects to be included has been determined based on the primary endpoint, namely the number of ovulations over 6 months (from month 9 to month 15). This design will cover to detect a 0.922 mean difference between placebo and SPIOMET arms. The standard deviation of 1.96 is based on previous evidence [14, 15]. The same difference and standard deviation are considered for potentially subsequent hierarchical comparisons (see the section “Trial design {8}”).

A sample size of 364 AYAs with PCOS [at least 180 of whom will be aged < 18.0 years at study start] is required using a 1:1:1:1 allocation ratio for placebo, PIO, SPIO and SPIOMET. The number of participants to be recruited is thus 91 per treatment arm (Table 5). Assuming a 27% dropout rate, approximately 266 patients (~ 66 or 67 per treatment arm) are estimated to complete the study.

**Table 5 Tab5:** Sample size and minimum detectable differences among comparison groups

Allocation ratio	1:1:1:1	

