#### Assessment of outcomes

##### Ovulatory function

Salivary progesterone will be centrally analysed at HSJD using an Enzyme-Linked Immunosorbent Assay (ELISA) [IBL-TECAN, Hamburg, Germany; intra- and inter-assay coefficients of variation (CVs) of 4.9 and 6.7%, respectively; salivary progesterone in the luteal phase, range: 87–550 pg/mL].

Saliva samples are a non-invasive, feasible method for monitoring progesterone levels across the menstrual cycle as they can be self-collected at home and stored in a home freezer for months before analysis [93]. Salivary progesterone concentrations are closely related to unbound serum progesterone [94]. This method has been previously used to assess ovulation rate in adolescents with type 1 diabetes and polycystic ovarian morphology [95, 96]; in one pilot study performed in HSJD, serum progesterone assessed by immuno-chemiluminescence, and salivary progesterone measured by the proposed method were highly correlated (*r* = 0.84; *p* < 0.0001; unpublished results). Two pilot studies performed in adolescent girls with PCOS have confirmed the reliability of salivary progesterone measurements [14, 15].

Information from salivary progesterone measurements and from menstrual diaries will be combined to infer ovulations and annualised ovulation rates. In the two previous pilot studies performed at HSJD [14, 15], with a similar ELISA method no longer available (Novatec, Immundiagnostica, Dietzenbach, Germany; intra- and inter-assay CVs < 10%), candidate ovulations were identified using a lower salivary progesterone cut-off of 99 pg/mL, as recommended by the manufacturer. All the ovulations that were confirmed by the above-mentioned two-step process were associated with salivary progesterone concentrations > 150 pg/mL. The progesterone cut-off derived from the ELISA assay to be used in the present study will be updated/rewritten when the new assay/method has been tested/validated. Candidate ovulations will be confirmed if the menstrual calendar mentions that menses did occur at least 2 weeks before and at most 2 weeks after obtaining the concerned saliva sample.

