### Methods in analysis to handle protocol non-adherence and any statistical methods to handle missing data {20c}

The handling of missing data will follow the principles specified in the ICH Topic E9 (CPMP/ICH/363/96), ICH E9 [110] and guidance on missing data [111] guidelines. The main analysis will include all randomised patients following the ITT principle, and thus, patients not completing the 6 months’ assessment period for the primary endpoint will be imputed. If patients have completed ≥ 80% of the 6 months assessment, then the mean value will be imputed for the rest of the missing observations. Otherwise, the 0 to 3 months of follow-up initial period after randomisation will be used for the imputations.

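### A cycle that ends in conception within a saliva window cannot count as an ovulation, and a pregnancy during treatment sends the rest of the primary count to imputation from months 0–3

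*Protocol article*

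**What the plan says.** Four statements in the protocol article bear on this point.

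- **Confirmation of an ovulation** (Ovulatory function). A candidate ovulation found from salivary progesterone is confirmed only if the diary shows that "menses did occur at least 2 weeks before and at most 2 weeks after obtaining the concerned saliva sample". No exception is made for a cycle that ends in pregnancy.
- **Stopping treatment** (section {11b}). "Criteria for discontinuing the allocated intervention are as follows: (1) pregnancy". The same section adds: "Discontinuation of the study intervention will imply discontinuation of the study and thus a dropout". Data collected up to that time are kept.
- **Missing data** (section {20c}). All randomised patients are analysed. If at least 80% of the six-month assessment is complete, a mean value fills the rest. Otherwise "the 0 to 3 months of follow-up initial period after randomisation will be used for the imputations".
- **What months 0–3 are expected to show** (Analysis of the primary outcome). The arms are expected to have similarly few ovulations in this first period.

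Saliva is collected in months 0–3, 9–12 and 12–15 only. The primary count covers months 9–15. Pregnancy tests are scheduled from month 0 to month 12. Section {22} sends pregnancies to a surveillance form for safety reporting. Nothing in the protocol links them to the primary endpoint.

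**The concern.** Each rule is reasonable alone. Together they mishandle an event that depends on the effect under test. The menses condition is there to corroborate a progesterone rise, but in a conception cycle the expected menses do not come. The strongest corroboration available, a pregnancy, therefore leads to rejection of the candidate. If the pregnancy occurs during treatment, the patient's later weeks are then filled from the period in which a treatment effect is least expected to be visible.

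Pregnancy requires ovulation, so more conceptions would be expected in arms that restore ovulation. Loss of counts through pregnancy would then tend to lower the primary mean in those arms. The trial commits itself to the estimands addendum of ICH E9 (section {20a}), yet the stated imputation rule handles this event like any other dropout.

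**Working it through.** **The plan's own figure.** Section {14} seeks to "attain 80% statistical power at two-sided 5% alpha level" and to "detect a 0.922 mean difference between placebo and SPIOMET arms"; "The standard deviation of 1.96 is based on previous evidence".

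- Normal approximation: n = 2 × (1.960 + 0.842)² × 1.96² / 0.922² = 71 per arm. The exact t-test gives 72.
- The stated 91 per arm is reached by multiplying: 71 × 1.27 = 90.2, rounded up to 91. Dividing gives 71 / 0.73 = 97.3, rounded up to 98.

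That difference is a separate matter. Here 91 and 0.922 serve only as the scale for the loss.

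**Which imputation branch applies.** 80% of six months is 0.80 × 6 = 4.8 months, reached at month 9 + 4.8 = 13.8. Treatment ends at month 12, when at most 3 / 6 = 50% of the window is complete. So a pregnancy that stops treatment always falls below 80% and goes to the months 0–3 branch, never to the mean-value branch.

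**What happens, by time of conception.**

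| Conception in | Conception cycle | Primary count (months 9–15) |
|---|---|---|
| Months 0–3 | In a saliva window; fails the menses condition | All imputed from months 0–3, which itself lacks the conception cycle |
| Months 3–9 | Outside any saliva window; not scored | All imputed from months 0–3 if she stops before month 9 |
| Months 9–12, treatment stopped | In a saliva window; fails the menses condition | Confirmed ovulations kept; missing part imputed from months 0–3 |
| Months 12–15 | In a saliva window; fails the menses condition | No treatment left to stop and no scheduled pregnancy test. If she stays in, later weeks without menses yield no ovulation. If she leaves, section {20c} applies: mean value after month 13.8, months 0–3 before |

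**Size.** The protocol gives no pregnancy rate, so these inputs are assumptions: 1–2 pregnancies in an arm of 91, and 1–3 ovulations lost per case. A lost ovulation means one that would have been counted had the conception cycle been accepted and the later weeks continued at the patient's later rate.

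- Fall in the arm mean = cases × ovulations lost / 91.
- Low end: 1 × 1 / 91 = 0.011, and 0.011 / 0.922 = 1.2% of the target.
- High end: 2 × 3 / 91 = 0.066, and 0.066 / 0.922 = 7% of the target.
- Standard error of a difference between two arms: 1.96 × √(2/91) = 0.29. The high end is 0.066 / 0.29 = 0.23 of it.

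**Effect on power** (t-test, all 91 per arm analysed, SD unchanged; 88.4% with no loss). The inputs are a net excess share of pregnant patients in SPIOMET and the ovulations lost by each.

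| Net excess | Lost per case | Difference left | Power |
|---|---|---|---|
| 1% | 1 | 0.912 | 87.7% |
| 2% | 3 | 0.862 | 83.9% |
| 5% | 4 | 0.722 | 69.6% |

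The last row is a stress test: a 5% net excess is about 4.5 of 91 patients. Nothing in the protocol supports a figure that high.

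**The case against.** The case against has real weight, and several of its points limit the finding.

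- **A reader might infer that a pregnant patient is scored as never having ovulated.** The protocol does not support that. Only the conception cycle is lost, and only in a saliva window. Data collected before discontinuation are kept, and no rule erases confirmed ovulations.
- **A reader might infer that every pregnancy leads to imputation from months 0–3.** That holds for pregnancies that stop treatment. In months 12–15, half of the primary window, there is no treatment to discontinue, and the mean-value branch is possible.
- **A reader might infer that the bias always runs against the better arm.** The rules apply equally to all arms. A pregnancy on placebo lowers the placebo mean and widens the difference. With one or two cases, the arm in which they fall is largely chance.
- **A reader might infer that months 0–3 was chosen because counts are low there.** The protocol says that it stands in for an assessment before randomisation, which might have deterred enrolment. Low counts are what it is expected to show.
- **Few cases are likely.** Sexually active patients must guarantee non-hormonal contraception, and at least 180 of the 364 are to be under 18. The months 0–3 rule reaches many other dropouts: 27% of 91 is about 25 per arm. One or two pregnancies add little to that.
- **The analysis plan may deal with it.** The protocol defers derivation algorithms to the SAP, where handling of pregnancy as an intercurrent event would commonly be set out.

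The last point does not dispose of the concern. The menses condition, the dropout rule and the imputation rule are all stated here, and together they give a wrong value for a conception cycle. That is a stated rule with a wrong result rather than detail left for later.

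**Conclusion.** The point holds as a minor defect in the primary endpoint rule. A conception cycle in a saliva window is scored as no ovulation when it certainly was one. A pregnancy that stops treatment also moves the unobserved part of months 9–15 to a source period expected to be low.

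Under the assumptions of 1–2 cases in one arm and 1–3 ovulations lost per case, the arm mean falls by 0.01–0.07, at most about 7% of 0.922 and less than a quarter of a standard error. The high end places every case in one arm. The direction against arms that restore ovulation is a tendency, resting on the dependence of pregnancy on ovulation. The protocol does not support a claim of certain bias or of material loss of power. The case for acting is that the value is plainly wrong and cheap to correct.

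**What to change.** 1. **Endpoint rule.** State that a cycle within an assessed saliva window that ends in a confirmed pregnancy counts as one ovulation without the condition of following menses. Date it from the last menses in the diary, the saliva series and the pregnancy test. The surveillance form should not be relied on for this, since section {22} does not list a conception date among its contents. Limiting the credit to the window in which the cycle falls keeps a conception at, say, month 5 out of the months 9–15 count.
2. **Intercurrent event.** Name pregnancy as an intercurrent event with its own handling of the later weeks. Where part of months 9–15 was observed before conception, use that observed rate instead of months 0–3. Where none was observed because conception came before month 9, use a model-based imputation with a sensitivity analysis. Carrying forward the patient's own on-treatment rate would not help in that last case, because the only saliva data she has are from months 0–3.
3. **Reporting.** Show pregnancies by arm beside the primary result.

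The cost is one or two sentences before database lock and a little more analysis work. Pregnancy stays a criterion for stopping treatment, and no clinical rule changes.

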#### Strategies to improve adherence to interventions {11c}

A face-to-face medical visit will be scheduled every 3 months for each participating AYA, for a total of 5 visits over 12 months to maintain a close contact, and to monitor adherence until the end of the active treatment phase. Adherence will be calculated as the ratio between the number of tablets prescribed and dispensed for the period between hospital appointments and the number of tablets returned by the patient at the following appointment. In addition, the Intake Table of the Patient Diary will be screened to check whether the aforementioned ratio fits with the information registered by the patient.

The aforementioned LIP sessions will be implemented by a trained research nurse during the same 5 quarterly visits over the same 12 months of active intervention [77]. In order to optimise adherence, the LIP will focus on strengths rather than on weaknesses; such an approach is known to raise treatment adherence [80].

In order to further improve adherence to the pharmacological and LIP interventions, patients will be contacted by phone between clinical visits, in order to check how they are doing.

#### Relevant concomitant care permitted or prohibited during the trial {11d}

Study participants cannot participate concomitantly in another clinical trial.

Prohibited concomitant use/prohibited medication: (1) oral oestroprogestogen contraception prior to (3 months) and during the entire study (18 months); (2) iodinated contrast agents; (3) caution must be exerted with the concomitant use of medications that may cause hyperkalaemia or metabolic acidosis, such as nonsteroidal anti-inflammatory drugs, including selective cyclooxygenase II inhibitors, angiotensin converting enzyme inhibitors, angiotensin II receptor antagonists and diuretics, especially loop diuretics.

#### Provisions for post-trial care {30}

After study completion (18 months), the participants will receive the best available treatment that their physician considers most appropriate.

### Outcomes {12}

#### Primary outcome

The primary outcome will be the number of ovulations on-treatment and post-treatment (ovulatory function) by salivary progesterone analysis for 12 consecutive weeks during two periods on-treatment (months 0–3, and months 9–12), and during one period post-treatment (months 12–15). Information from salivary progesterone and from menstrual calendars (recorded in the patient’s diary) kept by the patients will be combined to infer each ovulation.

#### Secondary outcomes

Clinical variables:Weight, height, BMI, waist to hip ratio (WHR), systolic blood pressure (SBP), diastolic blood pressure (DBP)Hirsutism score (modified Ferriman and Gallwey score) [22, 82]Acne score (evaluated using the Leeds Acne Grading Scale) [84]Menstrual regularityEndocrine-metabolic variables:Circulating androgens: total testosterone, SHBG, FAI (equivalent to free testosterone), and  androstenedioneLipids—total cholesterol, low-density lipoprotein (LDL-cholesterol), high-density lipoprotein (HDL-cholesterol), triglyceridesInsulinaemia: fasting and 2 h after an oral glucose load [oral glucose tolerance test (OGTT)]. Estimation of insulin resistance from fasting insulin and glucose levels using the insulin resistance homeostatic model assessment (HOMA-IR)Markers of inflammation and insulin sensitivity: us-CRP, C-X-C motif chemokine ligand-14 (CXCL14), HMW-adip, GDF15Epigenetic variable: circulating microRNA 451a (miR-451a) concentrationsImaging variables:
Cardiovascular risk: cIMT (ultrasound)Body composition: dual-energy X-ray absorptiometry (DXA)Abdominal fat distribution (subcutaneous and visceral) and hepatic fat (magnetic resonance imaging, MRI)Lifestyle assessment parameters, including changes in (1) imaging variables; (2) clinical variables; (3) endocrine-metabolic variables; (4) health behaviour assessed through a questionnaire on physical activity, eating behaviour and nutrition adapted from the Health Behaviour in School-aged Children (HBSC) questionnaire; (5) minimisation of adverse side effects and evaluation of the risk of eating disorders assessed through the Eating Disorder Screening questionnaire SCOFF and the first question of the Binge Eating Disorder Screener 7 (BEDS-7); only in case the risk is confirmed, then, the Eating Disorder Examination Questionnaire (EDE-Q) will be used; (6) adherence to the LIP (completion of preparatory task); (7) patient-reported outcomes (PROMs) on HRQoL, assessed through generic short form 36 health survey (SF-36) and PCOS health-related quality of life questionnaires (PCOSQ).Safety variables:Laboratory safety variables: blood count (haemoglobin, haematocrit, red blood cell count, white blood cell count, platelet count), electrolyte panel (sodium, potassium, chloride, calcium, phosphorus), urea, alanine aminotransferase (ALT), aspartate aminotransferase (AST), gamma-glutamyltransferase (GGT), creatinine, vitamin B12 and folic acidPregnancy testReport of AEsAdherence and acceptability:Adherence, calculated as the ratio between the number of tablets prescribed and dispensed for the period between two hospital appointments and the number of tablets returned by the patient at the following appointmentAcceptability of the tablet by the study patientsPROMs on HRQoL: assessed through SF-36 and PCOSQ

